## Abstract

**Introduction:**

Living donor kidney transplantation (LDKT) is the optimal treatment for most patients with end-stage renal disease (ESRD). However, there are numerous patients who cannot find a living kidney donor. Randomised controlled trials have shown that home-based education for patients with ESRD and their family/friends leads to four times more LDKTs. This educational intervention is currently being implemented in eight hospitals in the Netherlands. Supervision and quality assessment are being employed to maintain the quality of the intervention. In this study, we aim to: (1) conduct a cost-effectiveness analysis of the educational programme and its quality assurance system; (2) investigate the relationship between the quality of the implementation of the intervention and the outcomes knowledge, communication and LDKT activities; and (3) investigate policy implications.

**Methods and design:**

Patients with ESRD who do not have a living kidney donor are eligible to receive the home-based educational intervention. This is carried out by allied health transplantation professionals and psychologists across eight hospitals in the Netherlands. The cost-effectiveness analysis will be conducted with a Markov model. Cost data will be obtained from the literature. We will obtain the quality of life data from the patients who participate in the educational programme. Questionnaires on knowledge and communication will be used to measure the outcomes of the programme. Data on LDKT activities will be obtained from medical records up to 24 months after the education. A protocol adherence measure will be assessed by a third party by means of a telephone interview with the patients and the invitees.

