## Introduction

Living donor kidney transplantation (LDKT) is the optimal treatment for most patients with end-stage renal disease (ESRD) in terms of quality-adjusted life years (QALY), survival and cost-effectiveness.^1^ However, there is a significant number of patients who cannot find a living kidney donor and many patients first undergo dialysis before transplantation with a living donor kidney. Interventions are needed to improve access to LDKT.

Research has shown that knowledge of renal replacement therapies (RRT) and communication between patients and their social circle play an important role in the access to LDKT.^2^ Studies have shown that a home-based interventional programme had positive effects for patients with ESRD.^3–5^ In our transplant centre in Rotterdam, the Netherlands, we have conducted two studies on this home-based educational approach: one randomised controlled trial (RCT) and one cross-over study. The RCT among 163 patients on dialysis showed significant increases in knowledge and communication about LDKT among the patients in the experimental arm who received the home-based education compared with the standard care control arm. Furthermore, there were significantly more actual LDKTs in the experimental group compared with the control group (17 vs 4, p=0.003).^3^

The cross-over trial was aimed at patients who had not previously undergone RRT and who were eligible for transplantation. In the first phase, the experimental arm received the home-based education while the control group waited. In the second phase, the control group also received the education. This study also showed that there was a statistically significant increase in knowledge and communication regarding RRT among patients and invitees after receiving the home-based education. Of the 80 participants, 49 underwent RRT during the 2-year follow-up. Of these, 34 underwent a LDKT, of which 22 were pre-emptive.^4^

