## Methods and design

### Participants and procedure

The implementation study is being conducted in the following regions of the Netherlands: Rotterdam, Amsterdam, Nijmegen and Groningen.

The home-based educational programme is currently being implemented in eight hospitals in the Netherlands; four university transplant hospitals and four regional hospitals. Regional hospitals were included to reach those patients who are yet to start RRT and in this setting, this is the target population. In these hospitals, there is a large dialysis unit but no transplants are conducted. For these hospitals, the inclusion criteria are: ≥18 years of age, are eligible for transplantation and primary RRT required within the coming 12 months. In the regional hospitals, allied health professionals carry out the intervention. The four university hospitals incorporate both a dialysis unit and a transplant centre, therefore in this setting both patients who are yet to start RRT and dialysis patients are the target population. Eligible patients for these hospitals are required to be ≥18 years, currently undergoing RRT or required within the coming 12 months and eligible for transplantation. In the university hospitals, allied health professionals are accompanied by psychologists to carry out the intervention. The distinction between the university hospitals and the regional hospitals is in line with the protocols of the aforementioned cross-over study and the RCT. An estimate of the potential candidates for this implementation is about 50 patients per year per university centre and 20 patients per regional hospital. The implementation study will take 2 years.

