### Quality assurance

This study has also implemented a central quality assurance system. We hypothesise that the effectiveness is moderated by the protocol adherence of the team of healthcare professionals. In the implementation study, it might be possible that there are differences in the way teams and centres adhere to the protocol. Protocol adherence measures will be assessed by a third party by means of a telephone interview with the patients and the invitees. Patients and invitees are asked for their opinion and level of satisfaction regarding the way in which the intervention was delivered. Patients and invitees are asked to answer the 15-item TAM scoring list. Items are rated on a Likert scale (1 not at all to 5 very much). Only items that are rated with a 5 will be regarded as fully adherent. Items scored with a 1–4 will be regarded as non-adherent. The outcome of the protocol adherence will be associated with the gain in knowledge and communication skills. We will also look if there is a correlation between the protocol adherence and the amount of LDKTs. A part of the quality assurance is a training that all professionals who conduct the home interventions must take part in. During this training, issues are discussed such as: how to convey uniform and complete information to the patient, how to behave during the home visits, how to create an alignment of the goals of the home visit with the patients, how to assist the patient in inviting friends and relatives, how to deal with emotional moments, how to discuss delicate topics with respect to individual feelings and opinions and, finally, how to ensure no detrimental psychosocial effects of the education occur for the patients and his/her family/friends. All these aspects can be executed in different ways by the educators. A supervisor evaluates the home visits with each team separately every 6 weeks and discuss difficult cases. After these meetings the supervisor is graded by the educators through a 10-item questionnaire regarding the content of the teaching and the interpersonal delivery of the supervisor. Furthermore, the supervisor will bring together all educators for a so-called intervision meeting every 3 months. These intervision sessions are meant to discuss the home visits with each other in order to learn from each other and to keep the procedures similar.

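### The adherence–LDKT correlation pools patients not yet on RRT with dialysis patients; it should be stratified by RRT status at education and should also use LDKT activities

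*Protocol article*

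**What the plan says.** **Who is educated.** Under Participants and procedure, regional hospitals take adults who "are eligible for transplantation and primary RRT required within the coming 12 months". University hospitals take adults "currently undergoing RRT or required within the coming 12 months and eligible for transplantation", a mixture whose split is not given. In regional hospitals the educators are allied health professionals; in university hospitals psychologists join them.

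**What is recorded.** The abstract says "Data on LDKT activities will be obtained from medical records up to 24 months after the education". The Introduction also defines the outcome as LDKT activities, beside knowledge and communication.

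**What is analysed.** The Quality assurance section names only the completed transplant: "We will also look if there is a correlation between the protocol adherence and the amount of LDKTs". It makes no distinction by RRT status.

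**What is known about the pre-RRT group.** The Introduction describes the earlier study: "The cross-over trial was aimed at patients who had not previously undergone RRT and who were eligible for transplantation". It reports "Of the 80 participants, 49 underwent RRT during the 2-year follow-up", and then "Of these, 34 underwent a LDKT, of which 22 were pre-emptive". It does not say what happened to the others.

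**The cost model.** Under Model description, patients enter on haemodialysis, on peritoneal dialysis or by transplantation. Under Markov states, every listed state is a dialysis modality or a transplant. Under Markov model, programme costs and transition probabilities are the only things that differ between the two situations compared.

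**The concern.** The two groups are at different stages of disease. A dialysis patient without an LDKT at 24 months remains on the treatment that the programme hopes to replace. A patient educated before RRT may have reached 24 months with an LDKT, on dialysis, with a deceased-donor kidney, without needing RRT yet, or may have died. A pooled count of completed LDKTs reduces all of this to yes or no.

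Hospital type is tied to the patient group and to the make-up of the team. If adherence scores differ between regional and university teams, the planned correlation is partly a comparison of case mix.

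The result matters: under Hypotheses, a shown relationship between adherence and effects would make quality assurance an inseparable part of the programme. An association created or hidden by case mix would misinform that decision.

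The model raises a related question. Educated patients who do not start RRT use programme resources, yet no listed state holds them.

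**Working it through.** **1. The earlier pre-RRT study (Introduction).** Inputs: 80 participants, 49 with RRT in 2 years, 34 LDKTs, 22 of them pre-emptive.
- No RRT: 80 − 49 = 31; 31/80 = 38.75% (exact 95% CI 28% to 50%).
- LDKT among all: 34/80 = 42.5%. Pre-emptive share of LDKTs: 22/34 = 64.7%.
- LDKT after dialysis: 34 − 22 = 12; 12/80 = 15%. RRT other than LDKT: 49 − 34 = 15; 15/80 = 18.75%.

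**2. The earlier dialysis trial (Introduction).** Inputs: 163 patients; 17 LDKTs in the educated arm against 4. Arm sizes and follow-up time are not given. Assuming an even split, 17/81.5 = 20.9%; with 78 to 86 patients in the arm, 21.8% to 19.8%.

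**3. How case mix alone could produce an association.** Assume that adherence has no effect in either group and that the two earlier rates apply. The pooled difference between high- and low-adherence patients is then (gap in pre-RRT share) × (0.425 − 0.2086) = gap × 0.2164.
- Gap of 0.20: 0.20 × 0.2164 = 4.3 percentage points.
- Gap of 0.40: 0.40 × 0.2164 = 8.7 percentage points.

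The sign depends on which teams score higher, which is not known. The rates come from different studies, so this is an illustration and not an estimate.

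**4. How many patients may have no RRT at 24 months.** The 38.75% applies only to those educated before RRT. Reading the 20 per regional hospital as per year, there are 4 × 50 + 4 × 20 = 280 candidates a year.
- Only regional patients pre-RRT: 80/280 × 38.75% = 11%.
- Half the university patients as well: 180/280 × 38.75% = 25%.
- All patients: 39%.

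If the 20 covers the whole two years, the first figure becomes 80/480 × 38.75% = 6.5%.

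**5. Should patients without RRT at 24 months be excluded?** Two assumed settings, each with two equal adherence halves of pre-RRT patients, give opposite answers.
- *RRT start unrelated to adherence* (61.25% start). Take LDKT rates among starters of 79.4% and 59.4%, that is, 34/49 = 69.4% plus and minus 10 points. Starters only: odds ratio 2.63. All patients: rates 48.6% and 36.4%, odds ratio 1.66. The risk ratio is 1.34 either way.
- *Better education raises pre-emptive LDKT.* Hold LDKT after dialysis at 15% and other RRT at 18.75%; let pre-emptive LDKT be 37.5% against 17.5%, drawn from those with no RRT. All patients: (0.525/0.475)/(0.325/0.675) = 2.30. Starters only: (0.525/0.1875)/(0.325/0.1875) = 1.62.

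In the second setting exclusion weakens the association, because an LDKT is itself a start of RRT and restricting to starters selects on the outcome.

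**The case against.** The strongest objection is that pre-emptive LDKT was the commonest LDKT route in the earlier study, 22 of 34. A transplant-eligible patient not yet on RRT can therefore have an LDKT from the day of education, and the absence of one may well reflect on the education. This stands. A reader might infer that patients without RRT at 24 months cannot be scored fairly, or that counting them necessarily pulls the association towards zero. The Introduction contradicts the first, and step 5 shows that the second depends on an assumption the article does not make.

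Three further objections have weight. The article does not say why 31 patients had no RRT; death or loss is possible. The 2-year period belongs to a two-phase study whose control group was educated later, so it need not equal 24 months after education. And one sentence in a condensed article need not be the whole analysis; adjustment could be set out in a document not shown. What that leaves standing is that this article states a single pooled correlation and narrows the outcome to completed LDKT after naming a wider one elsewhere.

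On cost, a reader might infer that the programme cost is understated by 80/49 = 1.63. The article does not support that. It nowhere says that one programme cost is attached to each model entrant; under Costs, intervention costs are recorded per centre, which allows total spending to be counted. A fixed multiplier of 1.63 would also overcharge, because inflow is continuous and late starters enter the model later.

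**Conclusion.** The point holds as one of confounding and outcome choice. As stated, the correlation pools two populations with different LDKT opportunity, educated by differently composed teams, and uses a narrower outcome than the one the abstract and Introduction name. Its size is illustrative: 4 to 9 percentage points of spurious difference for gaps of 20 to 40 points in pre-RRT share, assuming the two earlier LDKT rates apply and the dialysis trial's arms were equal. The direction is open. The share of educated patients without RRT at 24 months could lie anywhere from about 6.5% to 39%, depending on the unstated case mix and on how the regional figure of 20 is read.

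No particular attenuation or loss of power is established, nor is any fixed understatement of programme cost. For the model, the firm observation is that the text lists no pre-RRT state, so the treatment of programme cost for educated patients who do not start RRT should be stated.

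Stratifying by RRT status does not remove the difference in team composition between regional and university hospitals within the pre-RRT stratum. That remains a caution in interpretation.

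**What to change.** - Stratify or adjust the adherence–LDKT analysis by RRT status at education, a baseline value already known from the inclusion criteria.
- Keep all educated patients in the denominator. Do not exclude those without RRT at 24 months.
- Analyse the recorded LDKT activities alongside completed LDKT.
- Describe status at 24 months as LDKT, other RRT, no RRT yet, or died.
- In the model, count the programme cost of every educated patient, including those who never start RRT, once and at the time it is incurred. Apply no fixed 2-year multiplier.

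This costs some analysis wording and one status variable derived from medical records already being collected. The downsides are less precision within strata and a supplementary outcome, donor steps, that is softer than a completed transplant.

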**Ethics and dissemination:**

Ethical approval was obtained through all participating hospitals. Results will be disseminated through peer-reviewed publications and scientific presentations. Results of the cost-effectiveness of the educational programme will also be disseminated to the Dutch National Health Care Institute.

**Trial registration number:**

NL6529

Strengths and limitations of this studyWorking with a state-transition model involves a trade-off between feasibility and transparency of the model and the level of details of real life conditions.We do not have a control group in the implementation study, we will use the reported effectiveness of a randomised controlled trial conducted previously.By making a dynamic state-transition model, we can model the prevalence and incidence of patients with end-stage renal disease, and consequently the capacity for the facility needs which has not been done before.We have high-quality data at our disposal.

## Introduction

Living donor kidney transplantation (LDKT) is the optimal treatment for most patients with end-stage renal disease (ESRD) in terms of quality-adjusted life years (QALY), survival and cost-effectiveness.^1^ However, there is a significant number of patients who cannot find a living kidney donor and many patients first undergo dialysis before transplantation with a living donor kidney. Interventions are needed to improve access to LDKT.

Research has shown that knowledge of renal replacement therapies (RRT) and communication between patients and their social circle play an important role in the access to LDKT.^2^ Studies have shown that a home-based interventional programme had positive effects for patients with ESRD.^3–5^ In our transplant centre in Rotterdam, the Netherlands, we have conducted two studies on this home-based educational approach: one randomised controlled trial (RCT) and one cross-over study. The RCT among 163 patients on dialysis showed significant increases in knowledge and communication about LDKT among the patients in the experimental arm who received the home-based education compared with the standard care control arm. Furthermore, there were significantly more actual LDKTs in the experimental group compared with the control group (17 vs 4, p=0.003).^3^

The cross-over trial was aimed at patients who had not previously undergone RRT and who were eligible for transplantation. In the first phase, the experimental arm received the home-based education while the control group waited. In the second phase, the control group also received the education. This study also showed that there was a statistically significant increase in knowledge and communication regarding RRT among patients and invitees after receiving the home-based education. Of the 80 participants, 49 underwent RRT during the 2-year follow-up. Of these, 34 underwent a LDKT, of which 22 were pre-emptive.^4^

Given these positive results, a home-based educational programme for patients with ESRD and their social network is currently being implemented in four regions in the Netherlands. Per region, a regional hospital and a university transplant hospital are implementing the programme. The regional hospitals will target patients who are yet to start RRT, while the university hospitals will target both these patients and dialysis patients. The educators organise the intervention in such a way that they will do ‘whatever it takes’, in line with one of the basic principles of multisystem therapy (MST), to make this event as patient tailored as possible.^6^ Supervision and quality assessment are being employed to maintain the quality of the intervention. The first aim of this study is to evaluate the cost-effectiveness of the education to support continued implementation. In this article, we present the study protocol of a cost-effectiveness analysis of the educational programme and its quality assurance system. The patient population, the standard care, the quality of the educations and the setting differ per hospital. Therefore, our second objective is to investigate the relationship between the quality of the implementation of the programme, as measured by protocol adherence, and outcome. Outcome is defined in terms of knowledge, communication and LDKT activities.

### Hypotheses

Previous research has provided convincing evidence that transplantation costs less, gives a better survival and a higher quality of life compared with dialysis.^7–9^ We therefore hypothesise that the relatively small incremental costs of the home-based educational programme should be cost-effective. Since it is desirable that in the future all waiting list patients can benefit from the effects of the home-based intervention, this programme should be part of standard care. Hence, a solid basis of the cost-effectiveness of that educational programme is warranted.

The second hypothesis is that higher protocol adherence among healthcare providers will be associated with more positive effects of the educational interventions. These effects include an increase in knowledge of renal disease and the treatment options, an increase in communication with family/friends about RRTs, an increase in living kidney donation activities and an increase in QALYs. If a relationship between protocol adherence and effects is shown, a quality assurance system should be an inseparable part of the educational programme.

The third hypothesis is that a full implementation of the educational programme leads to policy implications regarding care for patients with ESRD. Full implementation may affect the need for dialysis centres and transplantation facilities. By modelling the prevalence we can estimate the need for allocating the healthcare budget. We aim to present the outcomes of the model in a budget impact analysis (BIA).

Thus, the main aim of this article is to discuss the protocol of the cost-effectiveness study of the home-based educational programme and of the quality assurance programme which are currently being implemented in the Netherlands. Additionally, potential policy implications of our hypotheses are discussed in this article.

## Methods and design

### Participants and procedure

The implementation study is being conducted in the following regions of the Netherlands: Rotterdam, Amsterdam, Nijmegen and Groningen.

The home-based educational programme is currently being implemented in eight hospitals in the Netherlands; four university transplant hospitals and four regional hospitals. Regional hospitals were included to reach those patients who are yet to start RRT and in this setting, this is the target population. In these hospitals, there is a large dialysis unit but no transplants are conducted. For these hospitals, the inclusion criteria are: ≥18 years of age, are eligible for transplantation and primary RRT required within the coming 12 months. In the regional hospitals, allied health professionals carry out the intervention. The four university hospitals incorporate both a dialysis unit and a transplant centre, therefore in this setting both patients who are yet to start RRT and dialysis patients are the target population. Eligible patients for these hospitals are required to be ≥18 years, currently undergoing RRT or required within the coming 12 months and eligible for transplantation. In the university hospitals, allied health professionals are accompanied by psychologists to carry out the intervention. The distinction between the university hospitals and the regional hospitals is in line with the protocols of the aforementioned cross-over study and the RCT. An estimate of the potential candidates for this implementation is about 50 patients per year per university centre and 20 patients per regional hospital. The implementation study will take 2 years.

If patients have not been able to find living donor candidates in their social network, they will be asked whether they and their social network wish to receive home-based education from healthcare educators. The nephrologist explains to the patients that the educators will provide information about renal diseases, the different types of RRT and their impact on quality of life. Furthermore, the educators can help to discuss the possibilities of living donation within the social network of the patient. If the patient consents to the intervention in consultation with his/her nephrologist, the healthcare educators contact the patient to make an appointment for the first home session. Patients are supported in inviting their family/friends to the second educational session. After completion of the programme, an evaluation consultation is planned with the nephrologist. The number of patients who do not consent to participate in the study is recorded, as well as the reason for non-participation.

